### Randomisation

Following recruitment and baseline testing, centres were pair-matched according to the number of educators and children in attendance, geographical location and Indigenous status of the centre. Centres within each pair were then randomised to the *Jump Start* intervention or usual practice comparison group by a statistician, not involved in the recruitment or intervention delivery, using a concealed computerised random number generator. The statistician communicated the allocation to the Project Manager, who informed each ECEC centre. Recruitment and baseline assessments were conducted prior to randomisation by trained data collectors blinded to group allocation. The 18-month assessments will also be conducted by trained data collectors blinded to group allocation. To ensure all data collectors remain blinded during the assessment periods, a number of strategies have been put in place to minimise the risk of bias on treatment effect. All data collectors are blinded to study outcomes and hypotheses, and conduct assessments either in the intervention centres only or the usual practice comparison centres only. Educators have been asked not to discuss group allocation with data collectors. In addition, the primary outcome measure and methods, and where possible secondary outcome measurement methods, have been chosen to be as objective as possible in minimising potential for bias. Data collectors are only required to fit a monitor to participants for physical activity assessment, and an external trained assessor, blinded to group allocation, will code videos of the gross motor skills assessments.

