### Participant recruitment and eligibility criteria

The sampling frame comprised ECEC centres located in areas of disadvantage in NSW, Australia, according to the area location indices for socio-economic disadvantage (SEIFA) [38]. Centres were eligible if they were located in an area with a SEIFA index of relative socioeconomic disadvantage of less than or equal to 5 (lowest 50 %) [38] and had a minimum enrolment of five eligible consenting children. From the 74 eligible ECEC centres, 57 centres were approached and 44 centres were successfully recruited. One centre withdrew from the study due to not having the minimum number of consenting children (*n* = 3).

Children were eligible to participate in the evaluation components of the study if they were 3 years old, or turning 3 before the start of the intervention; attended at least 2 days a week at a participating ECEC centre; and were not likely to be enrolled in primary school the following year. All parents/caregivers of eligible children received a participant information sheet and a URL YouTube link to a recruitment video and were invited to provide written consent to participate. All educators working with 3 year olds in the ECEC centres were also invited to take part in the study and provide written consent to participation. Educators who are employed in centre-based ECEC services across Australia, and who are responsible for a group of children, are required by national regulations to hold at least a 12-month vocational qualification to work with children or be enrolled to complete such a vocational qualification [39]. Recruitment began in January 2015 and was completed in June 2015.

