### Power and sample size

Sample size and power estimates were based on the formula proposed by Murray [33] to adjust for a clustered (nested) cohort design. It is recommended that sample size estimates be based on the *a priori* minimum acceptable difference between groups to be considered meaningful [40–42]. Based on our experience and the changes observed in our pilot studies for accelerometer-based physical activity, we estimated this minimum acceptable difference to be 45 mins/day of total physical activity, which translates to an effect size (Cohen’s d) of 0.4. The 6-month Jump Start pilot [14] resulted in a Cohen’s *d* = 0.4 for counts per min, and the 6-month Jump Start translational pilot resulted in a Cohen’s *d* = 0.39 for percentage of time spent in LPA [43]. We therefore concluded that achieving an effect size ≥ 0.4 was realistic and our multi-component intervention strategies, with an increased intervention length and intensity compared to our pilot studies, would be expected to produce an effect size similar to or greater than these studies. For a two-tailed alpha = 0.05 and an intraclass correlation (ICC) of 0.01–0.05 our proposed sample size of 608 participants (304 per group) provides approximately 86 % power to detect an intervention effect of 0.4 or greater for the ICC range proposed.

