### Statistical analysis

#### Primary analysis

Analysis of the primary outcome will be conducted using a linear or generalized mixed model. The mixed model will contain a random effect for time and ECEC centre nested within group. Degrees of freedom will be altered manually in the code to adjust for the effect of clustering. These established procedures are well documented by Murray [33] and have been used previously by the authors to analyse a similar study in primary schools [62]. No interim analyses will be conducted before all data have been collected.

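### Centres are randomised within matched pairs, but the primary model names no pair term, so its standard error does not reflect the matching

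*Protocol article*

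**What the plan says.** Three parts of the protocol article bear on this.

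- **Randomisation:** after recruitment and baseline testing, "centres were pair-matched according to the number of educators and children in attendance, geographical location and Indigenous status of the centre". The next sentence begins "Centres within each pair were then randomised to the" and names the two arms. Allocation is therefore restricted: one centre of each pair goes to each arm.
- **Primary analysis:** "Analysis of the primary outcome will be conducted using a linear or generalized mixed model". The structure follows: "The mixed model will contain a random effect for time and ECEC centre nested within group". Then: "Degrees of freedom will be altered manually in the code to adjust for the effect of clustering". Neither pair, centre size, location nor Indigenous status is mentioned. Secondary analyses extends mixed models to the continuous secondary outcomes and adds no such term.
- **Power and sample size:** the formula is one chosen "to adjust for a clustered (nested) cohort design", and no gain from matching is claimed.

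On numbers, the recruitment section gives 44 centres recruited and adds: "One centre withdrew from the study due to not having the minimum number of consenting children". That leaves 43, an odd number.

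**The concern.** Matching aims to make the two centres of a pair alike, so that differences between pairs drop out of the arm comparison. A model with centre nested in group and no pair effect leaves those differences in its estimate of between-centre variance. If pairs are alike on the analysed outcome, the model's standard error is larger than the true sampling variation of the arm difference under this allocation. The interval is then wider than it need be, and the test rejects less often than its nominal 5%.

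The choice also fixes a number that the protocol says will be entered by hand. With 44 centres the between-centre degrees of freedom are 44 − 2 = 42 without pairs and 22 − 1 = 21 with them. With 43 centres they are 41, or 20 from 21 complete pairs. Unless the handling of pairs is settled beforehand, the choice between these could be made with the data in view.

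**Working it through.** **Inputs.** From the protocol: 608 children (304 per group), d = 0.4, two-sided alpha 0.05, ICC 0.01 to 0.05, stated power about 86%, 44 centres recruited. Derived: 608/44 = 13.8, about 14 children per centre (m). Assumed: r, the within-pair correlation of centre effects on the analysed scale, which equals the share of between-centre variance that the pairs explain.

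**Step 1, the plan's own power figure.** With g centres per arm and m = 304/g, SE = √{2[1 + (m − 1)ICC]/(m·g)} in SD units, with noncentral t on 2(g − 1) df. With g = 22, power is 99.5% at ICC 0.01 and 96.4% at ICC 0.05. The stated 86% is not reproduced. At ICC 0.05 it would need about 9 to 11 centres per arm. The number of centres planned when the figure was computed is not given, so this does not show the 86% to be wrong. Neither calculation counts on matching.

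**Step 2, the standard error.** Up to a common factor, the variance of the arm difference is

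- as estimated without pairs: ICC + (1 − ICC)/m
- true under matching: ICC(1 − r) + (1 − ICC)/m

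The SE ratio is the square root of the first over the second. Type I error is approximately 2[1 − Φ(1.96 × ratio)]. With m = 14:

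| ICC | r | without pairs | true | SE ratio | type I error |
|---|---|---|---|---|---|
| 0.01 | 0.3 | 0.0807 | 0.0777 | 1.02 | 4.6% |
| 0.01 | 0.5 | 0.0807 | 0.0757 | 1.03 | 4.3% |
| 0.05 | 0.3 | 0.1179 | 0.1029 | 1.07 | 3.6% |
| 0.05 | 0.5 | 0.1179 | 0.0929 | 1.13 | 2.7% |

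At r = 0 the ratio is 1 and type I error is 5%.

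**Step 3, simulation of centre means** (22 pairs, m = 13.8, 100,000 trials per cell; 42 df without pairs, 21 df with). At the planned d = 0.4, power is 95.6% or more in every cell either way, so the contrast hardly shows. To see it, the effect was rescaled so that the analysis without pairs has 86% power when r = 0. At ICC 0.05 (d = 0.32):

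| r | power without pair term | power with pair term | type I error without |
|---|---|---|---|
| 0 | 86.2% | 84.6% | 5.0% |
| 0.1 | 86.4% | 85.8% | 4.6% |
| 0.25 | 87.2% | 88.0% | 3.9% |
| 0.5 | 89.0% | 91.9% | 2.8% |
| 1 | 91.7% | 97.3% | 1.2% |

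With the pair term, type I error stays at about 5% throughout. At ICC 0.01 (d = 0.27) the differences are small: 86.0% without v 84.4% with at r = 0, 86.7% v 86.4% at r = 0.5, and 87.5% v 88.6% at r = 1.

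**Step 4, cost of the pair term.** The critical value rises from 2.018 (42 df) to 2.080 (21 df): 2.080/2.018 = 1.03, or 3%. The largest power loss in step 3 is 86.2 − 84.6 = 1.6 points, at r = 0.

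**The case against.** The strongest reply is that leaving out the pairs is a legitimate trade of variance against degrees of freedom. It brings no bias, and type I error stays at or below 5%. Matching used centre size, location and Indigenous status, not baseline activity, while the primary outcome is change in activity; r may be near zero. At ICC 0.01 the pair term gains nothing until r is above 0.5. All this stands, and it limits the size of the point.

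A second reply is that a journal article condenses, and that covariates may sit in a fuller document. That is fair for covariates. It is weaker for pair, because the Primary analysis section states the random effects and that structure does not fit the stated allocation. The Economic analyses section does speak of resampling paired centre-level costs and effects, but this most naturally means each centre's cost taken with its own effect, so it does not supply the missing term.

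A reader might infer three stronger things that the documents do not support:

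- *That the omission erodes the stated power.* The 86% counts on no gain from matching. Even without the pair term, effective matching raises power (86.2% to 91.7% in step 3).
- *That pairs are positively correlated by construction.* That is the aim of matching, not a guaranteed result.
- *That an unpaired centre lets the estimate be altered once allocation is known.* The model as written would simply keep that centre, the Per-protocol analyses section puts all centres in the intention-to-treat analysis, and the withdrawal is not dated relative to pairing. A rule is needed only once a pair term is added.

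**Conclusion.** The mismatch is real: centres are randomised within pairs, and the stated model has no term for them. Its effect is on precision and is conservative in direction. For r of 0.3 to 0.5 and about 14 children per centre, the standard error is 2 to 3% too large at ICC 0.01 and 7 to 13% too large at ICC 0.05. The corresponding type I error is about 4.3 to 4.6% and 2.7 to 3.6%. These figures rest on an assumed r and on the protocol's ICC range holding for the analysed outcome; at r = 0 there is no inflation. The result would remain valid, but part of the precision that matching may offer is forgone. The change is worth making because its cost is small and bounded, and because the degrees of freedom are to be set by hand.

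**What to change.** Add a random intercept for matched pair to the primary and secondary mixed models, keeping any centre without a partner in the analysis as its own stratum. Alternatively, enter the matching factors (centre size, location, Indigenous status) as covariates. State the degrees of freedom that go with the choice before the data are analysed: about 20 to 21 with pairs against 41 to 42 without, the latter reduced by the number of centre-level covariates if that route is taken. If the matching is to be left out deliberately, say so and give the reason.

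The cost is one model term and a sentence or two of text. No new data are needed, since pair and the matching factors are already known. The downside is the 3% rise in the critical value and the loss of at most about 1.6 points of power if matching turns out uninformative.

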### Theoretical framework for the intervention

The *Jump Start* intervention is based on Bandura’s Social Cognitive Theory [44], which has been used extensively in behaviour change interventions. Social Cognitive Theory posits that behaviour is learned, modified and sustained through the interplay of personal, behavioural and environmental factors. The intervention focuses on each factor and how they influence participation in physical activity. To address personal factors, the intervention seeks to increase the emphasis and valuing of children’s physical activity and motor skill development by ECEC educators and parents. To address behavioural factors, there will be a focus on developmentally appropriate activities that build behavioural and motor skills. Educators and parents will have some choice about how they implement some of the components, giving them ownership (control) over children’s learning and the scheduling of intervention sessions at the ECEC centre. The intervention will provide opportunities for educators to set developmentally appropriate mini-goals and provide a sense of achievement. Behavioural skills include goal-setting and self-monitoring of implementation by the educators and parents. Environmental factors will be addressed at both social and physical levels. The social level will incorporate the aforementioned values systems and interaction skills, and will include modifying existing policies and schedules, and using educators to model and reinforce positive attitudes towards physical activity and correct techniques for performing the motor skills. At a physical level, strategies include increasing access and availability to resources that will promote motor development and physical activity in structured and unstructured sessions.

The intervention focuses on the four processes suggested by Bandura [45] to enhance behaviour change (attention, retention, production and motivation). All components of the *Jump Start* intervention have been designed to address all four by: (a) including stimulus material and specific lesson activities that will engage and direct the attention of the educators, parents and children; (b) matching their cognitive and behavioural skill levels in content and pedagogy, and providing opportunities to enhance mastery experiences; (c) including incentives that are relevant, attractive and specified before the learning activities; and (d) emphasising perceived choice and control, as well as challenge, curiosity and mastery through activities that enhance intrinsic motivation, greater persistence, and higher satisfaction [46]. The intervention has been designed to target Social Cognitive Theory mediators which have been identified as mechanisms of behaviour change in physical activity interventions among educators and young children.

### Jump start intervention development

An intervention mapping exercise was conducted using the “working backwards” process developed by Robinson and reported in previous interventions [46, 47]. An example of this process for the Jump Out component of the intervention is found in Fig. 2. Briefly, this involves identifying the ultimate goal, mapping all the potential mediating pathways (referred to as Major and Sub-categories in the Figure), and identifying the individual behaviours at the origin of each causal chain of events. Following this, a theoretical framework is applied to develop the *Jump Start* intervention (in this case, Social Cognitive Theory [44]). Specifically, principles of Social Cognitive Theory were applied to generate potential intervention strategies (see far left-hand column in Fig. 2) for enhancing a specific aspect of the theory. For example, for increasing the value that educators place on gross motor skills and physical activity in young children in their Centre, a strategy would be to show educators how the *Jump Start* intervention links to important compliance and curriculum documents such as the Early Years Learning Framework and National Quality Standard [19, 48]. Included in this step is anticipating potential barriers educators may encounter and strategies they could adopt to overcome these barriers. The next step was to evaluate the completed intervention plan (as per Fig. 2) to check if opportunities were provided for the four key learning processes of attention, retention, production and motivation in every element of the *Jump Start* intervention. We also applied additional principles of intrinsic motivation developed by Lepper et al. [49], including competence, challenge, curiosity, control, context, cooperation and competition (referred to as the 7C’s by Robinson [47]), to ensure the messages and activities promoted intrinsic motivation of the targeted behaviours.

**Fig. 2 Fig2:**
[figure not shown]
Intervention mapping diagram for the Jump Out component of the *Jump Start* intervention. Similar mapping diagrams have been developed for each of the Jump Start components

Table 1 details the specific components of the *Jump Start* intervention. The *Jump Start* intervention has been contextualised for the ECEC settings by linking it to the sector’s frameworks and curricula (NQS and EYLF) [19, 48] and using sector-specific terminology. All resources and equipment needed to deliver the *Jump Start* intervention will be provided to intervention centres.

**Table 1 Tab1:** A description of the five components of the *Jump Start* intervention

Jump start component	Description of component	Who facilitates the component
Jump In	Structured gross motor lessons, which will be facilitated every day for approximately 20 min. This component focuses on one gross motor skill, across two lessons every fortnight for 13 skills. All skill lessons are repeated three times over the 18-month period. The skill experiences are based on fun, interactive and engaging games [28].	Educators
Jump Out	Provision of opportunities for children to practise the gross motor skills taught in the Jump In component every day. It provides opportunities for educators to engage with the children in physical activity and encourage the correct performance of the skills. Jump Out is predominantly child-led and educators respond to the child’s cues using a variety of intentional teaching methods.	Educators
Jump Up	Music-based activities designed to break up long periods of sedentary behaviour with high-energy physical activity. The children and educators will engage in two 3-minutes songs every day.	Educators
Jump Through	Activities designed to connect learning and movement [31]. This component aims to use movement to enhance the learning experience. This component will be facilitated twice a day using a range of fun and engaging strategies.	Educators
Jump Home	Opportunities provided to families to learn about Jump Start and for parents/caregivers to participate in the same activities at home that the children have been participating at the ECEC centre.	Parents/caregivers

### Educator training for the intervention

The *Jump Start* intervention is designed to be implemented by ECEC educators. Professional learning was delivered by a trained ECEC educator and provided to other educators through an intensive one-day professional learning session, as well as ongoing bespoke professional learning opportunities provided during the intervention period. An ECEC educator is ideally suited to deliver the professional learning as they have experience working with children in these settings and understand the day-to-day running of an ECEC centre [39]. The one-day intensive professional learning involved 6–8 h of face-to-face contact or virtual contact through teleconferencing technology, and covered background information and the philosophy behind the *Jump Start* intervention, reflection on current practices, content related to each component, opportunities to experience and practice delivery of each component, and a final reflection on how the *Jump Start* intervention could be integrated in the daily routines at the ECEC centres. Free on-going bespoke professional learning was also available to all educators, which focused on additional training in the specific components of the intervention. This additional training was conducted at face-to-face support visits or during the monthly support phone calls provided to all intervention centres.

### Comparison condition

The *Jump Start* intervention is being compared incremental to current usual practice in the ECEC sector. This includes the availability of resources from the *Munch and Move* healthy eating and gross motor skills program [50], which is freely available to all ECEC centres. *Munch and Move* offers online professional learning and support through health promotion officers from the local area health service.

### Strategies to limit attrition

Based on previous feasibility, acceptability and pilot studies of the *Jump Start* components [28, 30, 31, 35, 36], a number of intervention strategies will be implemented to limit attrition. Strategies include: face-to-face support visits and monthly phone calls with all *Jump Start* intervention centres, monthly newsletters providing activity ideas and support information, providing all intervention equipment and resources at no-cost to the *Jump Start* intervention centres, providing non-monetary incentives to the children (e.g. stickers) for completing assessment tasks.

### Outcome measures

Table 2 summarises the outcome measures assessed with children, educators and parents/caregivers. All outcome measures for children were assessed on-site at the ECEC centres.

**Table 2 Tab2:** Summary of the outcome measures assessed

Outcome measure	Source	Baseline	6-months	18-months
*Children*				
Physical activity^a^	Accelerometry	X	X	X
Gross motor skills	TGMD-2	X		X
Weight status	BMI	X		X
Bone strength	Sunlight MiniOmni Ultrasound Bone Sonometer	X		X
Self-regulation (including executive functioning)	Card Sort task	X		X
	Go No Go task	X		X
	[name] task	X		X
	Not This task	X		X
	Heads-Toes-Knees-Shoulder	X		X
Educator- and Parent-proxy report of children’s approaches to learning	Approaches to Learning scale [58]	X		X
Educator- and Parent-proxy report of children’s temperament	Temperament scale [59]	X		X
*Educators*				
Self-efficacy	Purposively-developed	X		X
Demographics	Purposively-developed	X		
*Parents/caregivers*				
Self-efficacy	Modified questionnaire [61]	X		X
Demographics (including child’s demographics)	Purposively-developed	X		

^a^primary outcome variable; *TGMD-2* Test of gross motor development 2, *BMI* body mass index

